No studies have so far analysed in detail whether improvement in dexterity reflects reduction of basic motor impairments or works by learning compensatory movement strategies. To date, there is a growing weight of evidence in favour of compensatory learning strategies (Kwakkel et al, 2004; Sunderland, 2005). For example, there are strong indications that motor recovery after cortical injury occurs to a large extent through behavioural compensation strategies, rather than via processes of true recovery alone (Kwakkel et al, 2004b; Sunderland, 2005; Geurts et al, 2005). Theoretically, behavioural compensation strategies in which deficits are taken over by motor control of the less-affected trunk are considered to be potential confounders in our understanding of ‘neural repair’ and related cerebral recovery after stroke (Kwakkel et al, 2004; Sunderland, 2005). For example, in one recent study of stroke patients, moderately to severely impaired subjects used compensatory strategies of the trunk to accomplish a pointing task, rather than trying to achieve restitution of the original arm function (Cirstea et al, 2000, 2003). Cortical changes detected by fMRI may therefore reflect alternative (compensatory) motor skill learning rather than restitution of stroke induced impairments. As a result, these studies fail to differentiate between ‘motor recovery based on true repair’ and ‘motor recovery based on using compensation strategies’. This has caused considerable difficulty in the interpretation of such changes in fMRI studies, apart from other potential confounding factors such as a lack of control over mirror movements, strength, precision and the timing of imaginary movements (motor paradigm) during fMRI scanning. Finally, understanding the observed adaptive behavioural movement strategies requires that the biomechanical changes of the musculoskeletal system are measured longitudinally. For this purpose, it is of vital importance to understand the relationship between parameters characterizing CNS function (such as TMS and fMRI) and parameters describing end-point mechanical behaviour and peripheral reflex-chain properties.

Project B1: fMRI/TMS

*Research questions:*

1. Are CIMT-induced gains reinforced by recruitment of cortical activation in the ipsi-lesional hemisphere compared to patients receiving usual care?

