2. Is it possible to explain the recovery of dexterity in the paretic extremity during the first 6 months post stroke from the changes in cortical activation found in the first 4 weeks on fMRI in M1, vPMA, dPMA and SMA cortices of infarcted and non-infarcted cerebral hemispheres in patients with primary ischemic middle cerebral artery stroke?
3. Are changes in fMRI patterns in the contra-lesional cortex (M1) related to the impact of cortico-spinal tract degeneration as established with TMS within the first week and at 6 months post stroke?
4. What is the predictive value of TMS parameters such as motor threshold, motor evoked potential (MEP) and the subsequent ‘silent period’ (cortical inhibition phenomenon) for functional outcome at 6 months?
5. Which muscles of the paretic limb (i.e., intrinsic hand muscles, finger and wrist extensors or upper arm muscles) are most sensitive and specific in predicting functional outcome at 6 months post stroke?

Project B2: kinematics

*Research questions:*

1. Can functional improvement of the paretic arm during the first 6 months be explained by behavioural strategies to compensate for deficits (e.g., bending and rotating the trunk) in a standardized reaching task?
2. What is the relation between kinematic changes observed during functional recovery and dynamic changes in cerebral motor networks?

Project B3: haptic robot

*Research questions*

1. How and to what extent do endpoint mechanical behaviour (at the wrist joint) and peripheral reflex chain properties change during follow-up after stroke?
2. Does CIMT or EMG-NMS affect endpoint mechanics and peripheral reflex chain properties?
3. How do endpoint mechanics relate to upper limb performance in executing a reaching task?
4. How are these parameters and changes in parameters in the course of time influenced by CMIT or EMG-NMS?

*2.3 Project C: longitudinal relations. Objective: analysing the longitudinal relations between the results of project B.*

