Relatively poor recovery profiles in terms of neurological deficits (FM-score, MI-arm score, somatosensory deficits and neglect) and ARAT may be associated with: 1) the use of compensation strategies (expressed as bending and rotating the trunk towards an object) and 2) the amount of contra-lesional activation in fMRI and TMS (i.e., recruitment of cerebral activity). Those patients showing a normalization of ARAT outcome (i.e. > 53 points) are expected to show: 1) normalization of kinematics and 2) focusing of cortical activity on the original physiological areas involved (i.e. M1, SMA, CC dPMA and vPMA) and intactness of corticospinal tract on TMS.

*Research question*:

How are improvements in dexterity longitudinally related to observed changes in neurological impairments, kinematics and biomechanics and to changes in cortical activation patterns as revealed by fMRI and TMS?

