A translated and adapted version of the Motor Activity Log will be used (Van der Lee et al, 2004), which contains the 14 original activities, 11 additional activities, and 1 optional activity chosen by the patient. The list of activities and the rating procedure are shown in Appendix 9. Reliability and validity of the MAL has been proved in a number of studies. (Van der Lee et al, 2004) The MAL will be administered to each applicant and, if available, their caregivers. It will be used to independently rate how well (11-point Quality of Movement [QOM] scale) and how much (11-point amount-of-use [AOU] scale) the paretic arm was used spontaneously to accomplish 30 activities of daily living outside the laboratory (Van der Lee et al, 1999; Uswatte et al, 2005).

*3.2 Project B: cortical reorganisation and compensation strategies*

Primary outcome measures:

fMRI:

focusing of cortical activity on the original physiological areas involved (M1, SMA, CC, dPMA and vPMA) during a standardized wrist flexion-extension movement

TMS:

intactness of corticospinal tract, by early presence of a Motor Evoked Potential (MEP) resulting from transcranial magnetic stimulation in three key arm muscles (*m abductor digiti minimi, m biceps brachii and m. extensor carpi radialis*).

Kinematics:

bending of the trunk during the standard reaching task, as recorded by a 3-D kinematics recording system

Haptic robot:

Velocity induced gain of the peripheral spinal reflex chain and its modulation to changing environmental conditions (damping) as assessed by haptic robotics, system identification and neuromuscular modeling

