Project B1: The numbers needed for an fMRI study depend on the signal intensity of the volumes of interest (VOI).Our calculation is based on fMRI measures of Brodmann areas 9 and 46, which are primary association cortices. In these areas, the fMRI activation is assumed to be more difficult than in primary motor and sensory cortices. Therefore, our power analysis uses a conservative estimate of the number of subjects needed. The mean increment of the intensity of the signal in VOI (%) and the standard deviation of the normal signal intensity have both been found to be 1.5, whereas delta 'n' (i.e., the normalized minimal difference between groups that is detectable with fMRI) is estimated to be 1.15. Calculation of the required sample size is based on the formula {N=[2*(z(1-Alpha/2)-z(1-Beta))raise to square*(var(n)/delta)] in which Alpha (preventing type I error) and Beta (preventing type II error) are set at 0.01 and 0.10, respectively. This leads to a sample size of 13 patients in both the control and experimental groups. Based on an expected drop-out rate of 10%, we would need at least 30 stroke victims.

Project B3: Considering the parameter with the largest variability, i.e. reflex gains, a worst-case calculation of sample size, based on earlier measurements on stroke patients using haptic robots, reveals that the number of patients that needs to be measured is 10 in each ‘arm’ of the study, for an alpha of 5% (preventing Type I Error) and a beta of 10% (preventing Type II Error). This calculation is based on a standard deviation of 0.17 Nms/rad. (Meskers et al 2006) The smallest detectable difference will then be 0.12 Nms/rad (two-tailed). Controlling for 10% drop-outs groups of 30 from project A1 en 30 of project A2 should be sufficient.

*5.3 Project C: longitudinal relations*

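### The Project B1 sample size is calculated for VOI signal increment, not for the stated fMRI primary outcome, and 13 per group does not follow from its own inputs

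*Protocol*

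**What the plan says.** Four places in the protocol bear on what fMRI is meant to measure.

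- **Section 3.2, primary outcome measures for Project B.** The fMRI entry reads "focusing of cortical activity on the original physiological areas involved (M1, SMA, CC, dPMA and vPMA) during a standardized wrist flexion-extension movement". It gives no index, unit or hemisphere.
- **Section 2.2, Project B1, question 1.** This is the only fMRI question that compares randomised groups: "Are CIMT-induced gains reinforced by recruitment of cortical activation in the ipsi-lesional hemisphere compared to patients receiving usual care". Question 2 is about explaining recovery and looks at "changes in cortical activation found in the first 4 weeks on fMRI in M1, vPMA, dPMA and SMA cortices of infarcted and non-infarcted cerebral hemispheres".
- **Section 2.3, Project C.** Patients whose ARAT normalises are expected to show "focusing of cortical activity on the original physiological areas involved (i.e. M1, SMA, CC dPMA and vPMA". Poor recovery is linked to "the amount of contra-lesional activation in fMRI and TMS (i.e., recruitment of cerebral activity". Here recruitment refers to the contralesional side; in B1 question 1 it refers to the ipsilesional side.
- **Section 5.2, power analysis for Project B1.** "Our calculation is based on fMRI measures of Brodmann areas 9 and 46, which are primary association cortices". The quantity is "The mean increment of the intensity of the signal in VOI", in percent, with mean and SD both 1.5. The normalized detectable difference is 1.15, alpha 0.01 and beta 0.10. The result is 13 per group, or at least 30 in total after 10% drop-out. The choice of region is defended as conservative because activation there is harder to obtain than in primary motor and sensory cortex.

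**The concern.** A sample-size statement should refer to the outcome it is meant to support. Here the outcome is a pattern (activity concentrated on named motor areas), the between-group question is about recruitment in one hemisphere, and the calculation uses a signal amplitude in areas outside the outcome's list. Nothing in the protocol connects the three.

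The defence offered in section 5.2 is about where the signal is measured. It says nothing about moving from an amplitude to a focusing measure, which will have its own variance and its own plausible group difference.

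Two things are at stake. A reader of section 5.2 would believe that B1 has 90% power for its primary outcome, which nothing in the protocol shows. And because amplitude and focusing need not agree, the protocol should settle which one answers the between-group question.

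**Working it through.** **Inputs, all from section 5.2, Project B1:** alpha 0.01, two-sided because the printed formula uses Alpha/2; beta 0.10, so 90% power; normalized difference d = 1.15; SD 1.5; stated result 13 per group. Assumption: normalized means in SD units.

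**1. Trying to reproduce 13 per group.**

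- Standard formula: n = 2(z₀.₉₉₅ + z₀.₉₀)²/d² = 2(2.576 + 1.282)²/1.15² = 29.76/1.3225 = 22.5, so **23 per group**. That is 46 in total, and 46/0.9 gives 52 with drop-out. One-sided, it is 20 per group.
- By two-sample t-test (noncentral t), power is 89.7% at 24 per group and 91.1% at 25, so **25 per group**.
- If 1.15 is a raw difference with SD 1.5: 29.76 × 2.25/1.3225 = 50.6, so 51 per group.
- The formula exactly as printed (minus sign, variance 2.25, difference not squared): 2(2.576 − 1.282)² × 2.25/1.15 = 6.6.
- Two non-standard readings come near the stated figure. With unit variance and an unsquared difference, 29.76/1.15 = 25.9, which is 13 per group only if N is the total. With d = 1.5 in place of 1.15, 29.76/2.25 = 13.2.
- The drop-out step is consistent: 26/0.9 = 28.9, so 29, stated as at least 30.

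The stated inputs, used in the standard way, do not give 13.

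**2. What 13 per group delivers for signal increment.**

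- Power at d = 1.15, normal approximation: Φ(1.15 × √(13/2) − 2.576) = Φ(2.932 − 2.576) = 64%. By t-test with 24 degrees of freedom it is **56%**. The stated beta implies 90%.
- With all 30 patients retained (15 per group), power is 72% by normal approximation and 65% by t-test.
- Difference detectable with 90% power, normal approximation: (2.576 + 1.282) × √(2/13) = **1.51 SD**.

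**3. What can be said for focusing.** No n or power can be calculated, because the protocol gives no index, SD or group difference. For scale only, assumed standardised differences at the same alpha and power need 120 per group (d = 0.5), 47 (0.8), 30 (1.0), 23 (1.15) or 14 (1.5) by the normal formula.

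**4. Whether the two quantities can part company.** Suppose activation rises equally inside and outside the named areas. Signal increment in those areas goes up; a measure of concentration on them does not move. One is positive and the other null. If the rise is confined to the named ipsilesional areas, increment, recruitment and focusing all point the same way.

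**The case against.** Only section 3.2 is headed as primary outcomes. The B1 questions and the Project C text are research questions and expectations, and different questions may use different fMRI summaries. The exact focusing index can be left to an analysis plan. The proxy region is openly declared. Project B is exploratory, the trials' ARAT outcome is untouched, and compensation is also studied through kinematics.

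Most of this stands, and it rules out stronger readings. A reader might infer that the protocol contains three rival definitions of the primary outcome; it does not, it contains one definition and a calculation that refers to something else. The missing CC in question 2, which covers "M1, vPMA, dPMA and SMA cortices of infarcted and non-infarcted cerebral hemispheres", is a subset used for a prediction question and no conflict.

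A reader might also infer that the definitions can give opposite answers. The documents do not support that: the divergence in step 4 is one positive and one null result, not significant results in opposite directions. Nor can its size be fixed. If focusing were taken as ipsilesional minus contralesional signal (an index found nowhere in the protocol) and only the ipsilesional signal rose by 1.15 SD, t-test power would be 26% to 83% for assumed inter-hemisphere correlations of 0 to 0.7, against 56% for the signal itself. Power could be lower or higher. Under an inside-versus-outside index, a bilateral rise within the named areas could count as focusing.

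What the objection does not reach is the power statement. Declaring a proxy region does not justify a proxy quantity, and an analysis plan cannot turn this calculation into one for the section 3.2 outcome.

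**Conclusion.** The concern holds in limited form. The B1 sample size refers to VOI signal increment in areas outside the outcome's region list, the primary outcome is focusing, and the between-group question is about ipsilesional recruitment. The stated 13 per group therefore gives no assurance about the primary outcome. For signal increment itself it is too small for the stated error rates: about 23 per group are needed (25 by t-test), and 13 per group gives about 56% power. These figures assume that 1.15 is in SD units and the test is two-sided at 0.01; reading 1.15 as a raw difference makes the shortfall larger (51 per group).

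That increment and focusing can lead to different conclusions is a logical inference. How often they would do so depends on an index the protocol does not give. It also does not follow that the B1 conclusion will be chosen after the scans are read, since a separate analysis plan may fix the index. The point should be corrected; it does not affect the ARAT comparisons in Project A.

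**What to change.** - **Section 3.2 and B1 question 1:** name one fMRI summary over one region set as the primary between-group comparison, and make the other summary secondary. Use the same term for it in both places.
- **Section 5.2, Project B1:** state that the calculation refers to VOI signal increment and not to that outcome. Correct the formula, and report either the power at 13 per group (about 56% by t-test for a difference of 1.15 SD) or the difference detectable with 90% power (about 1.5 SD by normal approximation). Relabelling 13 per group as the size for signal increment without this correction would endorse an unsupported figure.
- **For the chosen primary outcome:** either give a detectable difference with the SD it rests on, or call the between-group fMRI comparison exploratory.

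The cost is protocol wording and a short recalculation. No extra scans or patients are needed. The downside is that the stated precision for fMRI will look less favourable.

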# 4. Patients and Methods

*4.1 Recruitment*

Subjects will be recruited in equal parts from the 4 participating university medical centres (LUMC, VUmc, RUMC and UMCU).

Patients with a first-ever ischemic lesion in the territory of the MCA, verified by CT and/or MRI scan, will be asked to participate in the first week post-stroke. Patients will receive a Patient Information Letter (Appendix 1) which will explain the background and methods of the study.

After given consent, patients will be randomized. This will include an intake procedure, containing the first assessment of outcome variables. Concealed allocation will be effectuated with sealed opaque envelopes.

The intensity and content of all therapies applied will be recorded in a patient log-book. All groups will receive usual care in terms of lower limb training. Changes in arm and hand function will be measured at fixed times by questionnaires and clinical tests.

*4.2 Coding of the patient data*

After inclusion of the patients into the study each patient will receive a 5 digit code, consisting of a code for the hospital of origin and the first three digits of the patient number. Data processing will take place using the coded patient information.

*4.3 General inclusion criteria*:

- first-ever ischemic lesion in the territory of the MCA, verified by CT and/or MRI scan;
- mono or hemi paresis as determined by a National Institute of Health Stroke Score (NIHSS) ≤ 4
- age between 18 and 80 years;
- able to comprehend and to communicate (MMSE score > 22 )
- written or oral informed consent;
- able to sit for 30 seconds without support;
- demonstrate sufficient motivation to participate in an intensive rehabilitation treatment programme for 3 weeks.

*4.4 Exclusion criteria*

- receiving recombinant tissue plasminogen activator (rTPA, or alteplase) with positive effect
- pacemaker or other metallic implants;
- upper extremity orthopaedic limitations that would affect the results;
- not being able to communicate (i.e. < 4 points on the Utrecht Communication Observation, UCO; Pijfers et al, 1985)
- being disoriented with regard to time and place (i.e., a Mini Mental State Examination (MMSE) score of 22 points or less) (Kwakkel et al, 1999).
- Botulinetoxine injections or medication intake that may influence upper limb function in the previous 3 months
- TMS: a history or family history of epilepsy, craniotomy and/or polyneuropathy
- fMRI: not being able to extend the wrist beyond 10 degrees and the fingers beyond 20 degrees.

*4.5. Allocation to each of the projects:*

#### Project A: early intervention

Project A1: (n=60) Patients with an upper limb deficit with an initially favourable prognosis (NIHSS arm score of 3 or 4 and/or ability to extend the wrist ≥ 10º) will be randomised into 2 groups:

- CIMT and conventional therapy.
- conventional therapy.

Project A2: (n=120) Patients with an initially poor prognosis for recovery of dexterity ((NIHSS arm score of 1 or 2 and/or inability to extend the wrist ≥ 10º) will also be randomized into 2 groups:

- EMG- NMS and conventional therapy;
- conventional therapy.

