###### Primary outcome measure: effect of the intervention

ARAT:

The Action Research Arm Test (ARAT) will serve as the primary measurement of outcome in both A1 and A2 EXPLICIT trials. The ARAT test is a performance test which assesses the ability to perform gross movements and the ability to grasp, move and release objects differing in size, weight and shape is tested. (Lyle, 1981) The original test consists of 19 items, rated on 4-point ordinal scales (0 to 3). By removing 4 items, a hierarchical 1-dimensional scale has been constructed (Van der Lee et al, 2002). The ARAT has been shown to be valid, reliable and responsive (De Weerdt et al, 1985; Van der Lee et al, 2001). The minimal clinically important difference (MCID) will be set at about 10% of the range of the scale, i.e. 6 points (Van der Lee et al, 1999). For project A2, return of dexterity will be defined as 10 points or more on the ARAT (Kwakkel et al, 2003).

Secondary outcome measures: detecting confounders, comparing groups and tracing changes per patient in time (see appendix)

Ashworth Score (AS)

The Ashworth score is a clinical test by which muscle tone is assessed manually around elbow and wrist.

Wolf Motor Function Test

An extended test of motor function. It is performed only at 3 and 6 months follow up.

Barthel Index

A widely used scale assessing performance of activities of daily living. The Barthel index is scored by the assessor without the need of physical presence of the patient

Frenchay Arm Test (FAT)

A five point scale to test arm function

National Institute of Health Stroke Scale (NIHSS):

A graded neurologicalexamination rating speech and language, cognition, visual fielddeficits, motor and sensory impairments, and ataxia. (Goldstein et al, 1997)

Motoricity Index-arm and leg (MI):

This test will be used to measure strength in upper and lower extremities (Collin et al, 1990). Higher scores represent greater strength in the upper limb. This instrument reliably and validly assesses the presence of paresis in stroke patients by testing 6 functions rated from 0 to 100 points for each limb (Collin et al, 1990; Kwakkel et al, 1999).

Brunnstrom Fugl Meyer arm/hand test (FM)-arm:

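### The A1 and A2 entry rules are not mutually exclusive: half of the score-by-wrist combinations qualify for both trials, no rule decides between them, and the NIHSS half appears to conflict with the wrist half.

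*Protocol*

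**What the plan says.** Section 4.5 (Project A) defines two trials by prognosis. A1 (n = 60, CIMT) takes patients with an "initially favourable prognosis (NIHSS arm score of 3 or 4 and/or ability to extend the wrist" by at least 10 degrees. A2 (n = 120, EMG-NMS) takes patients with "NIHSS arm score of 1 or 2 and/or inability to extend the wrist ≥ 10º". Neither this section nor any other says what happens when the two criteria disagree.

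Three other places bear on the split:

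- Section 4.3, general inclusion: "mono or hemi paresis as determined by a National Institute of Health Stroke Score (NIHSS) ≤ 4". It does not say whether the limit applies to the arm item or to the total score.
- Section 3.1, NIHSS entry: a graded examination whose listed contents include "motor and sensory impairments, and ataxia". The direction of scoring is not stated. For the Motoricity Index, in the same list, the protocol does state that higher is better.
- Section 4.1: "After given consent, patients will be randomized. This will include an intake procedure, containing the first assessment of outcome variables".

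Section 5.1 sizes A2 on a probability of about 6% that poor-prognosis patients regain dexterity, and on a 12% difference in favour of EMG-NMS.

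**The concern.** A1 and A2 are separate trials with different interventions, sample sizes and outcome definitions: a 6-point ARAT difference in A1, and an ARAT of 10 or more at 6 months in A2. The rule in 4.5 is all that separates them. If one patient can satisfy both rules, the trial entered depends on who recruits, and four centres may decide differently.

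A second difficulty lies inside each rule. A scale that rates deficits would normally give more points to a worse arm. A1 nevertheless groups scores of 3 or 4 with the ability to extend the wrist, both as signs of a favourable prognosis. If more points mean a worse arm, the two halves of each rule describe opposite patients.

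At stake are the meaning of the labels *favourable* and *poor*, the match between the patients enrolled in A2 and its 6% planning figure, and whether another group could reproduce the study populations.

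**Working it through.** The protocol states no figure on this point, so there is none to reproduce. The check lists every combination of arm score (1 to 4) and wrist extension (yes or no): 4 × 2 = 8.

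**Step 1. The rules as written (section 4.5)**

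| NIHSS arm score | Extends wrist ≥ 10° | *and/or* read as *or* | *and/or* read as *and* |
|---|---|---|---|
| 1 or 2 | yes | A1 and A2 | neither |
| 1 or 2 | no | A2 | A2 |
| 3 or 4 | yes | A1 | A1 |
| 3 or 4 | no | A1 and A2 | neither |

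Each row covers two scores. Under *or*, 4 of 8 combinations meet both rules. Under *and*, none meets both, but 4 of 8 meet neither. An arm score of 0 lies in neither band: under *or* the wrist alone decides, and under *and* the patient has no trial.

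**Step 2. Would exchanging the NIHSS bands help?**

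Put 1 or 2 with A1 and 3 or 4 with A2. Under *or*, scores of 1 or 2 without extension and scores of 3 or 4 with extension now meet both rules: again 4 of 8. Under *and*, those four meet neither. The overlap comes from the conjunction; the direction of the score only decides which patients fall into it.

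**Step 3. What share of patients could be affected?**

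The documents give no joint distribution, so the inputs here are assumptions. Let s be the share of patients with a score of 1 or 2 (30% to 70%), a the probability of wrist extension given a score of 1 or 2, and b that probability given a score of 3 or 4. With the rules as written,

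share meeting both = s × a + (1 − s) × (1 − b).

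*If a higher score is worse* (a at least as large as b):

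- a = 0.9, b = 0.1: 90% for any s
- a = 0.8, b = 0.2: 80% for any s
- a = 0.6, b = 0.2: from 0.7 × 0.6 + 0.3 × 0.8 = 66% to 0.3 × 0.6 + 0.7 × 0.8 = 74%
- a = b = 0.5: 50%

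*If a higher score is better* (values of a and b exchanged):

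- a = 0.1, b = 0.9: 10% for any s
- a = 0.2, b = 0.8: 20% for any s
- a = 0.2, b = 0.6: from 0.7 × 0.2 + 0.3 × 0.4 = 26% to 0.3 × 0.2 + 0.7 × 0.4 = 34%
- a = b = 0.5: 50%

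The share is thus 50% to 90% on one direction of the scale and 10% to 50% on the other. It is zero only if score and wrist sign never disagree in the sense that section 4.5 intends.

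**The case against.** The strongest reply is that the reversal is not proven. No section states the direction of the arm score. The limit of 4 in section 4.3 does not settle it either: a ceiling used to identify a paresis fits a score on which higher is better at least as well. On that reading 4.3 and 4.5 agree, concordant patients go cleanly to one trial, and only discordant patients overlap. This stands. The reversal is likely from section 3.1 and from the clash with the wrist criterion, but it remains conditional, and so does any statement that most patients are affected. The overlap itself does not depend on it.

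Several stronger readings are tempting but lack support:

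- *The inclusion rule admits patients without paresis, because 0 satisfies the limit.* The criterion itself names a mono- or hemiparesis, and A1 requires an upper limb deficit.
- *A total score of at most 4 contradicts an arm score of 3 or 4.* It would restrict entry severely, but the two are arithmetically compatible. The fault is that the item is not named.
- *Patients are randomised before they are classified.* Section 4.1 is ambiguous about the order, and 4.5 defines the groups before randomising within them.
- *The standard deviation used for A1 no longer applies.* Section 5.1 takes it from 102 first-ever MCA stroke patients and names no favourable subgroup.
- *A2 will enrol patients who already have dexterity, and its control rate will rise by a known amount.* Nothing links 10 degrees of extension or an NIHSS score to an ARAT value. The protocol gives neither the share of such patients nor their recovery rate.

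It is also fair to say that the treatment comparison within each trial is not biased. Patients are randomised after entering A1 or A2, whichever trial they enter.

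**Conclusion.** The point holds in this form. The overlap follows from the text of section 4.5 alone: 4 of 8 combinations qualify for both trials, or for neither if the conjunction is read strictly, and nothing in the protocol resolves them. This is a stated rule that fails to separate two trials; it is not a detail that could be left to an analysis plan.

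The conflict between the NIHSS half and the wrist half is well supported but conditional on higher meaning worse. If so, the double-eligible patients are the concordant ones (mild arm with extension, severe arm without), probably the most common. The number of patients affected cannot be derived from the documents; the range of 10% to 90% rests wholly on the assumed inputs above.

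The damage is to the target populations, to reproducibility across centres, and to the basis of the 6% control rate in A2. That rate presupposes a poor-prognosis group, which the rule does not isolate. Internal validity of each randomised comparison is untouched.

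**What to change.** Reconcile sections 4.3 and 4.5 so that every eligible patient belongs to exactly one trial:

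1. Define the split either on a single criterion that both rules already contain, or on both criteria with an explicit rule for patients in whom they disagree. Say where an arm score of 0 belongs, if such a patient can enter. Exchanging the NIHSS bands alone is not enough (step 2).
2. State the direction of the NIHSS arm score, and check that both halves of each rule point the same way.
3. State in 4.3 whether the limit of 4 refers to the arm item or to the total.
4. State in 4.1 that the classifier is assessed and recorded before the envelope is opened.

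Which clinical cut-off to use is for the investigators to decide. Once it is fixed, they should confirm that the 6% in section 5.1 comes from a group defined in a comparable way.

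The cost is a short eligibility amendment, best made before recruitment starts. The NIHSS is already in the assessment schedule. Wrist extension has to be judged anyway to apply the present rule, but it has no line of its own in that schedule, so a field on the entry form may be needed.
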